### *Primary Hypothesis*

We hypothesize the Interruptive CDS would be more effective at prompting in-person suicide risk assessment than Non-Interruptive (20% compared to 5%). Thus, we needed at least 75 patients in each arm to achieve 90% power with 5% probability of type I error.

---

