### *Secondary Outcomes/Endpoints*

Secondary trial outcomes include rates of thirty-day episodes of suicidal ideation, suicide attempt, rates of documented suicide risk assessment in clinical notes, psychiatric hospitalization, or emergency department utilization related to mental illness and/or suicide risk.

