### *Participant Timeline*

Randomization, interventions, and assessments all occur within each study encounter with no follow-up or additional interventions for either study participants (practitioners) or patients.

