#### *Auditing*

Study data will be analyzed by the PI and study team every three months for 1) continued validity of VSAIL to predict suicide attempt; 2) proper functioning of the VSAIL model [e.g., ensuring all predictors continue to be calculated appropriately for patients]; 3) rates of suicidal ideation and suicide attempt in patients randomized in the study. Because this study necessitates close collaboration with providers receiving BPAs, the study team will have monthly small-group meetings with providers in study sites at VUMC to assess for problems or perceived AEs related to the study protocol, though none are anticipated.

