### **10.0 Statistical Considerations**

In consultation with the study biostatistician ([name]) and Learning Health System ([name]), the study team determined the following power analysis.

On average at a predicted risk threshold of 2% predicted risk (the highest risk tier in settings without universal screening), 6 patients per day are anticipated in the highest risk tier. Randomizing half to the intervention arm and half to the comparator arm and 15 patients a week per arm, we anticipate 20% of the BPA prompts will be associated with face-to-face affirmation compared to 5% in the comparator arm, which means we need 75 patients in each arm to achieve 90% power with 5% type I error, 200 total, which will require fewer than six months to accumulate. Because prior suicide attempt is rare in this cohort based on diagnostic code ascertainment, simple randomization as above is justified.

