## **12.0 Follow-up and Record Retention**

The study will last six months.

As per IRB policy VI.B, all study data will be maintained for six (6) years from the date of the last use of study Protected Health Information (PHI) - at the conclusion of the trial period to identify patients in need of outcome data collection (which is based in EHR queries only).

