*Informed Consent – Post-trial qualitative evaluation*

For those providers who choose to participate, we will email each participant the link to RedCap eConsent form in advance of the interview. The RedCap eConsent framework allows participants the ability to download a copy of their signed consent form. At the start of the interview session, we will review the elements of the informed consent and give participants an opportunity to ask questions of the researcher. During this consent conversation, providers will be reminded that participation is optional and that they may choose to withdraw at any time without any consequences.

*Confidentiality*

Data will be collected from the EHR and stored securely in the VUMC Data Center on servers owned by the study team for later analysis. These systems are designed to securely store Protected Health Information and include encrypted storage, multifactor authentication, and both physical (locked doors, secure facility) and technical (active directory user authentication) controls. Protected Health Information, while necessary to conduct study analyses, will never be exported from these servers or shared.

Data to be collected include the VSAIL-produced probability, the predictors for that probability including historical counts of diagnoses, demographics (age, sex, race, zip code), medication counts, visit utilization (counts of outpatient, inpatient and emergency department visits) for the preceding five years. We will also collect documented and coded suicidality including suicidal ideation (a single

ICD10 code) and suicide attempt (a reference set of ICD10 codes used by our team and others from the CDC Center for National Health Statistics). We will also collect decision support usage statistics included face-to-face screening rates (the Columbia SSRS), and responses to the BPA: 1) "intent to screen" based on the alert; 2) "already screened for suicidality in this visit"; 3) "I disagree with this alert". Additional data will be collected from the same EHR data to evaluate secondary outcome and process metrics following the randomization: emergency department utilization; psychiatric consultation; documentation of suicide screening in clinical notes.

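### Thirty-day suicidal ideation is counted from a routine-care diagnosis code that the randomised alert may itself help to generate, so an arm difference cannot by itself be read as harm or benefit

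*Protocol*

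**What the plan says.** The Secondary Outcomes/Endpoints section states: "Secondary trial outcomes include rates of thirty-day episodes of suicidal ideation, suicide attempt". The Confidentiality text in section 13.0 fixes the source: "We will also collect documented and coded suicidality including suicidal ideation", with ideation defined by one ICD-10 code. Section 12.0 describes "outcome data collection (which is based in EHR queries only", and the Participant Timeline provides for "no follow-up or additional interventions for either study participants (practitioners) or patients". The protocol therefore contains no assessment of ideation made in the same way in both arms.

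Under Prediction and Randomization and under Recruitment, check-in triggers the risk score and then the randomisation, so the index visit comes after allocation. Section 2.0 says that screening in these settings is irregular or absent. The Interventions text under section 6.0 expects the alert to lead to screening that might not otherwise take place. Section 10.0 gives the planning contrast: "we anticipate 20% of the BPA prompts will be associated with face-to-face affirmation compared to 5% in the comparator arm".

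Under Auditing, the study team reviews every three months "rates of suicidal ideation and suicide attempt in patients randomized in the study".

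**The concern.** A diagnosis code for ideation records two things together: that the patient had suicidal thoughts, and that someone found out and wrote it down. The trial randomises something intended to change the second. Allocation precedes the index visit, and nothing in the outcome's wording sets aside a code entered at that visit. An alert that works as hoped could therefore raise coded ideation in the Interruptive arm while leaving the patients no different. Randomisation does not protect against this, because the difference in detection arises after allocation and as a result of it.

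What is at stake is how the secondary outcome can be read. An excess in the Interruptive arm could be better detection or worse patient state. Equal rates could conceal a true reduction offset by more detection. The three-monthly audit uses the same kind of rate, so a rise in it could reflect more asking and not more risk.

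**Working it through.** **Inputs from the protocol.** Assessment rates s = 20% (Interruptive) and 5% (Non-Interruptive), from the Primary Hypothesis, Sample Size and section 10.0. These are hypothesised responses to the prompt. Their ratio is 0.20/0.05 = 4.0 and their difference is 15 points. Section 10.0 gives both 75 per arm and 200 in total (100 per arm at 1:1). Both sizes are used here only to turn rates into counts; whether they agree with each other is a separate matter. The only ideation figure is a number needed to screen of 23 (section 2.0).

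**Assumptions, because the protocol gives no values.**
- p is the true prevalence of ideation, identical in both arms. The range is 1/23 = 4.3% to 30%. Reading the number needed to screen as a prevalence is itself an assumption, since the protocol defines that term differently.
- q is the probability that an ideating patient who is asked gets the code.
- b is the probability that an ideating patient who is not asked gets the code anyway, for example at another encounter within thirty days.

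**Formula.** Coded rate = p × [s·q + (1 − s)·b]. The spurious difference between arms is 0.15 × p × (q − b). It is positive whenever q > b, and zero only if q = b.

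**Ratio of coded rates.** p cancels.

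| q | b | Interruptive | Non-Interruptive | Ratio |
|---|---|---|---|---|
| 1 | 0 | 0.200p | 0.050p | 4.00 |
| 1 | 0.10 | (0.20 + 0.08)p = 0.280p | (0.05 + 0.095)p = 0.145p | 1.93 |
| 1 | 0.25 | (0.20 + 0.20)p = 0.400p | (0.05 + 0.2375)p = 0.2875p | 1.39 |
| 0.5 | 0.25 | (0.10 + 0.20)p = 0.300p | (0.025 + 0.2375)p = 0.2625p | 1.14 |

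**Absolute size at its largest (q = 1, b = 0).** The gap is 15% of p.

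| p | Coded rates | Gap (points) | Expected cases, 75 per arm | Expected cases, 100 per arm |
|---|---|---|---|---|
| 4.3% | 0.87% vs 0.22% | 0.65 | 0.65 vs 0.16 | 0.87 vs 0.22 |
| 10% | 2.0% vs 0.5% | 1.5 | 1.5 vs 0.38 | 2.0 vs 0.5 |
| 20% | 4.0% vs 1.0% | 3.0 | 3.0 vs 0.75 | 4.0 vs 1.0 |
| 30% | 6.0% vs 1.5% | 4.5 | 4.5 vs 1.1 | 6.0 vs 1.5 |

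**What one trial would show (100 per arm, q = 1, b = 0).** Counts are treated as two independent binomials. At p = 4.3% the Interruptive count is higher with probability 51%, tied 40% and lower 9%. At p = 20% it is higher with probability 88%. The chance of a spurious result significant at 5% by Fisher's exact test is about 0% at p = 4.3%, 10% at p = 20% and 23% at p = 30%.

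**The case against.** Several points on the other side are sound.

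- **20% versus 5% is not a rate of asking.** It is an expected response to the prompt. One of the response options is only an intention to screen, the same tool sits behind the icon in both arms, and section 7.0 leaves clinicians free to screen anyone. The ratio in actual asking may be below 4, so 4 is a ceiling under the protocol's hypothesis. A reader might infer that the design makes one arm ask four times as often; the protocol does not say so.
- **A difference is not certain.** A reader might infer that the arms will differ by construction. The difference holds only in expectation and only if q > b, and at this sample size it may be invisible.
- **A narrower figure is tempting but not sourced.** Suppose 10% to 20% of asked patients disclose, and add a 4.3% background to both arms. The ratios are then 0.0635/0.0485 = 1.31 and 0.0835/0.0535 = 1.56. The arithmetic is right, but the disclosure share has no source in the protocol and the background again rests on the number needed to screen.
- **The audit is not stated to be by arm.** A reader might infer a false safety signal against the Interruptive arm. The Auditing text gives neither a split by arm nor a threshold, so that reading is unsupported. What remains is that a pooled rate would also rise with screening uptake.
- **The protocol states no harm or benefit reading of ideation, and code windows are often left to an analysis plan.** The first part is true. The second does not dispose of the point, because the protocol itself names the outcome, its thirty-day period and its code source, and as written these mix detection with patient state.

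Small counts do not answer the point either. They make a significant artefact unlikely, but they do not make the outcome interpretable.

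**Conclusion.** The concern holds in a limited form. Coded thirty-day ideation is open to differential detection, with the expected direction upward in the Interruptive arm, and the protocol contains nothing to prevent or flag it. The size depends on quantities the protocol does not give. The expected ratio is between 1 and 4, and the absolute gap is at most 15% of true prevalence: 0.65 points at 4.3% and 4.5 points at 30%. That is under one case to a few cases at 75 to 100 per arm. The conclusion rests on the inference that asking raises the chance of a code, and on the 20% versus 5% hypothesis being roughly realised as a difference in asking. It supports the statement that an arm difference in this outcome cannot by itself be read as harm or benefit. It does not support the statement that the trial will show a difference. The point merits a change in the protocol, but it concerns a secondary outcome and leaves the primary comparison untouched.

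**What to change.** In Secondary Outcomes/Endpoints, split the ideation item in two:

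1. Ideation codes entered at the index encounter, reported descriptively as a detection measure (screening yield). Being assessed is itself a result of allocation, so a yield per patient assessed should not be offered as a randomised comparison.
2. Thirty-day ideation compared between arms, counting only codes from encounters after the index visit. State that some detection effect remains, since patients identified at the index visit may have more later contact or codes carried forward.

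Under Auditing, show index-visit and post-index ideation as separate lines, keep both visible, and review attempts separately, so that a rise in detection is not mistaken for a change in patient risk. Index-visit ideation should not be removed from the audit.

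The cost is a few sentences of protocol wording and one filter on the encounter identifier. The downside is fewer events in the between-arm ideation outcome, and a bias that is reduced but not eliminated.

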### *Interventions*

For patients randomized to the Interruptive VSAIL-prompted BPA, the Neurology MD clinician responsible for care in that encounter (determined in the usual course of care) will receive a BPA that shows the VSAIL score for that patient, e.g., 95th percentile of risk which correlates with 3 out of 100 people like this one having a suicide attempt within 30 days. The BPA also shows the last face-to-face screening with the Columbia Suicide Severity Rating Scale (CSSRS), if one exists, with a link to that screening document itself. The BPA prompts an opportunity to "Document" or "Not

Protocol Version #: 4

Protocol date last updated: 11/9/2023

VUMC IRB #210865

Important (1)

**Automated Suicide Risk Screening**

Vanderbilt AI has reviewed your patient's chart and noted risk factors placing them at elevated risk of suicide (VSAIL score: 95th percentile). We did not find a recent suicide risk screening in the record.

**Current risk score:** 95th percentile, 8 out of 100 patients like this one would have a suicide attempt in 30 days without prevention. [What does this mean?](#)

**Last face-to-face screen:** HIGH risk 18 months ago

This alert does not fire for all providers. It is part of a randomized trial. [Click here for more information.](#)

Time taken: 2/5/2021 1543

**Columbia Suicide Severity Rating Scale**

1. Wish to be Dead (within the past month)

Acknowledge Reason

**Figure 1: VSAIL-prompted BPA, fake data used here (Interruptive Arm)**

Document" a new CSSRS instrument at that time if providers choose to do so. Finally, providers are able to share either i) Intent to Screen; ii) Disagreement with the BPA; or iii) that screening has already taken place. See Figure 1 for the visualization of this BPA.

Dismissing the BPA (bottom right of Figure 1) leaves the Storyboard icon present in the eStar view, identical to the Non-Interruptive Arm described below. Hovering the mouse over the Storyboard icon reproduces the BPA alert and clicking on it permits the same functionality in the BPA as shown in Figure 1.

For patients randomized to the Non-Interruptive Storyboard Only Prompt (Non-Interruptive Arm), the provider will see an unobtrusive icon in the left side of the eStar window, the "Storyboard". The Storyboard is always present in eStar within an individual patient view. Hovering the mouse over the Storyboard icon reproduces the BPA alert and clicking on it permits the same functionality in the BPA as shown in Figure 1.

The VSAIL score will be available for all patients regardless of predicted risk tier in the study settings in the eStar flowsheet for equipoise but will not be pushed to providers outside the intervention arm. That is, providers who see value in the VSAIL risk score will be able to see it in eStar if they seek it out in the flowsheet.

[figure not shown]

Providers screening for or otherwise aware of VSAIL-predicted risk will have full discretion to treat suicidality clinically. The management of suicidality will follow standard of care at VUMC.

**Figure 2: Storyboard icon (Passive Arm and "dismissed" BPA view)**

Patients will experience routine care until providers screen for suicidality which they might not otherwise do without the VSAIL-prompted BPA for those identified at highest risk. That screening will take the form of the validated CSSRS or provider-chosen alternative (e.g., Patient Health Questionnaire-9 or direct questions about suicidal thinking posed by providers in their own way, the latter is consistent with known best practices to screen for suicidality in a direct and caring way; best practices do not dictate a single accepted screening instrument).

### *Discontinuing Interventions*

Because the trial interventions occur at a single decision-making time point within a single study encounter, discontinuing interventions will not apply. The participating practitioners might dismiss/ignore the alerts or they might act on them. This decision is the primary study outcome, as above.

### *Adherence to Intervention Protocols*

Adherence to the primary intervention outcome, decision to assess suicide risk, will be measured through direct interaction with the study decision support tools (see Interventions above). A secondary measure of adherence will be measuring whether suicide risk assessment is documented in clinical notes written as per routine clinical care in encounters in study settings during the trial period.

### *Relevant concomitant care and interventions*

Decision to act on study CDS or not is left to practitioners in study settings. Any concomitant care is permitted at any point in the trial and during study encounters.

### *Participant Timeline*

Randomization, interventions, and assessments all occur within each study encounter with no follow-up or additional interventions for either study participants (practitioners) or patients.

### *Sample Size*

We hypothesize the Interruptive CDS would be more effective at prompting in-person suicide risk assessment than Non-Interruptive (20% compared to 5%). Sample size calculation indicates at least 75 patient encounters are needed in each arm to achieve 90% power with 5% probability of type I error.

### *Recruitment*

Because of the pragmatic nature of this RCT, enrollment/randomization occurs at the time of check-in for routinely scheduled clinical care. No additional recruitment will be conducted. The rate of encounters is also stable as clinics tend to operate with consistent rates of clinical visits based on numbers of providers working in clinical settings.

---

### *Post-Implementation Evaluation*

We will analyze the BPA utilization data routinely collected within the Epic EHR to identify providers who encountered the BPA in regular patient care during the study period. We will select a representative sample of encounters based on the BPA utilization data and contact providers through a general announcement to recruit up to 30 providers for follow-up semi-structured interviews. We will follow up as needed with the group of providers who meet inclusion criteria.

This study evaluates usage of a novel decision support system that does not exist in usual neurologic workflow. Providers might voice concerns or dislike of

the system itself, issues related to suicide prevention practices in general in Neurology might be raised. No data specific to that provider's performance or practice will be collected that might increase risk of confidentiality. Safeguards to lessen this risk include deidentifying participants and redacting any identifying names inadvertently mentioned in interview sessions. Supervisors of participating employees will not be made aware of responses or decisions to participate. All data will be de-identified and all names will be changed to pseudonyms. All responses will be reported in aggregate.

Individual interviews will be conducted remotely via VUMC-approved secure HIPAA compliant video conferencing platform (e.g., Teams), audio/video recorded and transcribed, and last 30-60 minutes. Recordings will be stored on VUMC-approved secure servers (VUMC OneDrive or Sharepoint) and only authorized study personnel will have access.

Participants who complete an interview will be compensated with a \$50 electronic Amazon gift card which they will receive via email no later than one week after the interview.

## **7.0 Risks**

This protocol presents minimal risks to participants. Adverse events are not anticipated. Risks include discomfort among both providers and patients in discussing the sensitive but important topic of suicide. The risk model is not perfect and might not identify risk in those who are at risk – it is not intended to preempt providers screening any patient (or all patients) for suicidality if they choose to do so. The risk model might also identify risk in those not at risk, leading to questions of suicide screening being asked unnecessarily.

## **8.0 Reporting of Adverse Events or Unanticipated Problems Involving Risk to Participants or Others**

### *Harms*

The PI is responsible for monitoring study data, assuring protocol compliance, and conducting safety reviews. Because of the pragmatic nature of the study interventions (CDS decision aids), adverse events or other problems are not anticipated. In the unlikely event that such events occur, unanticipated problems involving risks to subjects or others that are i) serious, ii) unanticipated, and iii) possibly or definitely related to research procedures will be reported immediately to the PI, and in writing within 7 days to the VUMC IRB. The PI will apprise fellow investigators and study personnel of such adverse events that occur during the conduct of this research project through regular study meetings. Continuing review reports will be submitted annually to the IRB summarizing study progress, adverse events, complaints about the research or withdrawals, and any protocol violations.

We will follow the VUMC Human Research Protections Program (VHRPP) guidelines that require investigators to promptly notify the IRB within 7 days of

the occurrence when such unexpected Adverse Events (AEs) occur. These are events that could possibly be related to the intervention, or occur more frequently or are more severe than anticipated. VHRPP requires that any AE that is unexpected and related or possibly related to the research be reported. Adverse events not meeting this definition will be reported at the time of continuing review.

Unanticipated problems involving risks to subjects or others will be reported immediately, within twenty-four (24) hours of their discovery to the PI, and in writing within 7 days to the IRB. The PI will apprise fellow investigators and study personnel of all AEs that occur during the conduct of this research project through regular study meetings. Annual reports will be submitted by the study coordinator to the responsible IRBs summarizing study progress, AEs, complaints about the research, and any protocol violations.

